*Data collection*: Four semi-structured questionnaires have been developed and pretested. They include household, smoker, spouse and child questionnaires. The household questionnaire is for the household and comprises sociodemographic variables, number of family members, identifying the smokers, number of rooms, ventilation, distance from the road, type of road, any other source of air pollution within 500 m, organic and inorganic waste disposal, cooking fuel used, ventilation in the kitchen, use of mosquito coils, incense sticks, and the presence of pet animals. The smokers’ questionnaire will determine smoking habits, age of initiation of smoking, types of tobacco product used, money spent on tobacco per week, quit attempts, frequency and place of smoking within home, smoking when children are around, nicotine dependence score, awareness of harmful effects of second hand smoke, and who influences smokers the most. Nicotine dependence has been assessed by the Fagenstrom scale. The spouse questionnaire will consist of exposure to second hand smoke at home, practice of indoor smoking, ventilation in the kitchen, exposure to second hand smoke outside the home, cleaning habits, cooking practices, and medication use. The child questionnaire will consist of domains on reports of second-hand exposure at home and outside, history of respiratory morbidity in the past 6 months and history of hospital admission. For older children above 12 years the domains will also consist of history of tobacco use, age of initiation, and awareness regarding harm of second hand smoke. Standard methods of measurement of weight and height will be taken of the smoker, spouse and child. Blood pressure of the smoker and spouse will be measured by an electronic sphygmomanometer in a seated position after ensuring that the person is relaxed. If the reading is ≥140/90 mmHg the measurement will be repeated after 30 min and the average of the two will be taken. In order to measure FeV1/FeV6 the smokers will be instructed to take a deep breath and blow hard and long (6 seconds) till a beep is heard. The mouth should be sealed around the disposable mouthpiece. The measurement will be noted down by the health worker. We will also measure SHS through the air pollution monitor within the home which will measure particulate matter of size 2.5 microns and is a marker for the presence of SHS in the home. The device will be charged and left in the home for recording for 6-8 hours at an elevated place. The machine will record PM 2.5, 10 PM. The sensor will record the readings every 5 minutes and the output will be in the form of a graph. After downloading in the evening it will be given in the next house. This will be done at 6, 10, and 16 months respectively (

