**Smoker**				
Smoking within homes (self-reports)		✓	✓	✓
Fagenstrom nicotine dependence score		✓	✓	✓
No of cigarettes smoked daily		✓	✓	✓
No of persons who have quit			✓	✓
Blood Pressure		✓	✓	✓
BMI		✓	✓	✓
Fev1/Fev6		✓	✓	✓
*Air pollution	PM 2.5	✓	✓	✓
	PM 10	✓	✓	✓
	CO _2_	✓	✓	✓
Women	Cotinine	✓	✓	✓
Child	Cotinine	✓	✓	✓
BMI	Child	✓	✓	✓
Resp. Infection	Child	✓	✓	✓
	Woman	✓	✓	✓
Process evaluation	In depth interview			✓
	FGD			✓

A door-to-door initial survey will be conducted following a training to the data collectors. After ascertaining the households where the male member smokes the interviews of the smoker, wife/close female relative, and child will be conducted. The interviews will be conducted separately for the husband and wife/close relative who is a woman. After the interview, Fev1/FeV6 ratio among the smokers will be assessed with the Vitalograph COPD-6 screener device. The women and child of the household will be asked to keep the urine sample in a sample bottle provided which is then placed in an auto seal pouch. These samples will be collected from all the houses and transported to the laboratory by maintaining cold chain at a temperature between 2-8 degrees C. The urinary cotinine levels among the women and children of the smoking households will be assessed in this urine sample. The cotinine levels will be assessed among the spouse of the smoker or among a woman who stays at home for a longer duration and a child up to 18 years of age. If there is more than one child in the house, the youngest child older than 1 year will be chosen. All houses may not have children; therefore, it is necessary to take both women and children’s cotinine levels. This would also be an important advocacy tool as the children’s cotinine levels can be used to influence the smoker. The urine cotinine level will be measured at 6, 10, and 16 months with the help of Cal biotech’s ELISA kit which will measure cotinine levels by ELISA (solid phase competitive ELISA). The test was calibrated and standardised in a pilot study among households of smokers and non-smokers and differences ascertained.

Quality of data collected will be ensured by training and retraining of the data collectors. The data collection forms are provided.
^
40
^
^,^
^
41
^ The laboratory tests will be carried out after validation. Data entry will be done with back up and range check-ups will be done for data values.

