In the next two months home visits will be conducted to paste the smoke free home stickers or distribute the calendars and reinforce the message of not smoking within homes and to get widespread recognition of the movement. Based on the findings of the baseline survey customized messages to quit will be delivered. The SHG-ASHA combined will also communicate the results of the cotinine levels and 2.5pm to the household members. The cotinine levels among the children and women will be an especially powerful tool to motivate and influence men to quit smoking within the homes and then to quit ultimately. If they express an interest to quit, they will be referred to the nearest urban primary health center for tobacco cessation. The influencers will be contacted again to encourage the smoker to quit smoking within home and to quit. Creating a movement and making “not smoking within the house an acceptable sociocultural norm” is the objective. At the end of the intervention as part of the dissemination activity smoke free homes declaration meeting for all community members in the presence of political leaders will be conducted.

*Control arm*: The other arm will get the standard of care which would include the routine programs which are being run by the government as part of the national tobacco control program such as training of health and social workers, NGOs, school teachers, and enforcement officers; Information, Education, and Communication (IEC) activities; school programmes; monitoring of tobacco control laws; coordination with Panchayath Raj Institutions for village level activities; and setting-up and strengthening of cessation facilities including provision of pharmacological treatment facilities at district level. Periodic assessments will be done at 10 and 16 months.

Health workers will conduct end-line surveys soon after the intervention and six months after the intervention in the intervention and control arm with the same questionnaire, urinary cotinine measurement and SHS measurement with an environmental sensor. Thus the measurements will be at 6, 10 months and 16 months respectively.

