### Outcomes

**
*Primary and secondary*
**

The primary outcome is SHS exposure at homes at 10 months and 16 months as assessed by the change in mean urine cotinine levels among women and or children of the smoker at the individual level. The secondary outcomes will include individual level self-reports of smoking within homes, particulate matter 2.5, harm reduction (reduction in the number of cigarettes smoked), quitting of smoking, blood pressure, Fagenstrom Nicotine dependence score, and comorbidities. Individual level assessment of Fev1/Fev6 will also be carried out with handheld spirometry considering a cut off of 73% to be indicative of COPD which is also a secondary outcome. Forced expiratory volume in 1 second (FEV1) is the maximum amount of air that the subject can forcibly expel during the first second following maximal inhalation.
^
46
^ Similarly, forced expiratory volume in 6 seconds (FEV6) is the volume of forcibly exhaled air measured during 6 seconds
^
47
^ which can be measured by handheld spirometry.

Cluster level assessment of 2.5 particulate matter in homes will also be done with air quality monitors. Monitoring and assessing intervention in terms of development of a training booklet, educational material, number of meetings organized, proportion of self-help group members in the area participating and inviting local self-government members to participate.

In order to understand the reasons for success and failure, in-depth interviews of men who have successfully quit smoking within homes, quit smoking completely, ASHAs, and health workers will be conducted. Focus group discussions of wives of smokers who quit smoking within homes and those who reduced the number of cigarettes will be conducted.

*Data analysis and statistical plan*: Data will be entered electronically on a secure file storage system and password protected. Data will be anonymised by assigning a unique identification number to each smoker. Outcome data will be reported in accordance with the Standard Protocol Items: Recommendation for Intervention Trials (SPIRIT). All the smokers will be included in the analysis regardless of reduction in smoking within homes.

**
*Participant flow*
**

30 clusters will be randomly assigned into two groups and will receive intended intervention and will be analyzed for primary outcome of urinary cotinine. For each group losses and exclusion of clusters and individual participants will be recorded (
Figure 1).

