*Baseline data*: The baseline data will be presented for both clusters and individuals as the risk of chance imbalances are greater with clusters.

*Numbers analyzed*: We plan to analyze 30 clusters with at least 300 indoor smokers in each arm. The urine cotinine of the women and children will be obtained from 300 women and or children in each arm. The indoor home values of 2.5 PM will be obtained from 300 households in each arm. Similarly, the lung function values as indicated by FeV1/FeV6 will be assessed among 300 each in the intervention and control group.

*Outcomes and estimation*: The difference in mean cotinine levels among the clusters in the intervention and control group with 95% CI will be estimated. The intracluster correlation coefficient for each outcome will be reported. Adjusted estimates of clustering will also be provided. Cox’s proportional hazards will be calculated for quitting, harm reduction, blood pressure values. This is to determine the effectiveness of an intervention based on partnering with women’s SHG’s to reduce indoor tobacco smoking by measuring urinary cotinine levels.

A repeated-measures ANOVA will be used to compare the mean urinary cotinine concentration between groups, before and after intervention.

Analysis for self-reported quit rates will be assessed by a Cox proportional hazards model. Generalised linear mixed effect models will be used to test between cluster differences from baseline to each follow up period for each outcome indicator.

We will use an intention to treat approach in analysis. A multilevel model will be used for analysis using the generalized linear mixed effect model which will also adjust for individual covariates. Key variables will be measured at baseline and then compared between arms to check balance; and if both arms are unbalanced with respect to any relevant factors, which can happen given that the unit of randomization is the cluster instead of the individual, those factors will be adjusted for in the final analysis so as to address potential confounding. Analysis for SHS exposure rates and quit rates will be assessed by a Cox proportional hazards model.

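### Cox models are named for blood pressure, harm reduction and second-hand smoke exposure, which have no event or event time, and nothing says whether they or the mixed models govern

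*Protocol article*

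**What the plan says.** All references are to the protocol article.

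- **Cox models.** Under Methods, Outcomes, the Outcomes and estimation paragraph and the text following it name Cox three times. First: "proportional hazards will be calculated for quitting, harm reduction, blood pressure values". Then: "Analysis for self-reported quit rates will be assessed by a Cox proportional hazards model". Finally: "Analysis for SHS exposure rates and quit rates will be assessed by a Cox proportional hazards model".
- **Mixed models.** Directly after the second of these it says: "Generalised linear mixed effect models will be used to test between cluster differences from baseline to each follow up period for each outcome indicator". A multilevel model with individual covariates is promised a little further on.
- **What the outcomes are.** The Primary and secondary text gives "harm reduction (reduction in the number of cigarettes smoked"), with no threshold. It defines SHS exposure, the primary outcome, by change in mean urine cotinine in the women and/or children. Blood pressure is listed as a secondary outcome. Under Data collection it is a sphygmomanometer reading; if it is at or above 140/90 mmHg, "the measurement will be repeated after 30 min and the average of the two will be taken".
- **When they are seen.** The text on end-line surveys states: "Thus the measurements will be at 6, 10 months and 16 months respectively". The first of these is the baseline. Table 1 lists "No of persons who have quit" and ticks it at the two post-intervention surveys only.

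**The concern.** A Cox model takes each participant's time from an origin to a defined event, or to censoring. Nothing in the article defines an event, origin or censoring rule for blood pressure, cigarette number or exposure. An analyst following the text would have to invent a cut-off, an event and an event time, each of which changes the result. The only times available are the survey dates, so any times used would reflect the survey calendar.

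The sentence on mixed models then gives the same outcomes a second analysis with a different effect measure: a mean difference or odds ratio instead of a hazard ratio. With no order of precedence, the choice could be made after the data are seen. For quitting, a first-event model and a model of status at each survey also answer different questions once some quitters relapse.

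**Working it through.** **1. Does each outcome assigned to Cox have an event and an event time?**

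| Outcome | How the article describes it | Event defined? | Possible times |
|---|---|---|---|
| Blood pressure | A reading; 140/90 only triggers a repeat measurement | No | Surveys at months 10 and 16 |
| Harm reduction | Fall in number of cigarettes, no threshold | No | Same |
| SHS exposure | Change in mean cotinine; if read as yes/no, a state that can reverse | No | Same |
| Quitting | Quitters recorded at the two follow-ups | Natural candidate: first recorded quit | Same |

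For the first three rows the Cox model lacks its response variable. Only quitting supplies a candidate event.

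**2. Can a Cox model of first recorded quit be used with two visits?**

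The article gives no quit rate or hazard ratio, so these are assumptions: constant hazard, true hazard ratio 2.0, and control quit probability p of 5% to 40% over the 10 months from baseline (month 6) to month 16. The follow-ups fall 4 and 10 months after baseline. The control hazard is λ = −ln(1 − p)/10 per month.

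Example at p = 0.40:
- Control, quit by the first follow-up: 1 − 0.6^0.4 = 0.185.
- Intervention, quit by the first follow-up: 1 − 0.6^0.8 = 0.335.
- On the complementary log-log scale the ratio is ln(1 − 0.335)/ln(1 − 0.185) = 0.4087/0.2043 = 2.0.

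So a discrete-time complementary log-log model recovers the hazard ratio from grouped times. A simulation with 40,000 per arm, independent individuals and no relapse gave these estimates of the hazard ratio:

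| Control quit probability | Cox, Breslow ties | Cox, Efron ties | Complementary log-log |
|---|---|---|---|
| 5% | 2.02 | 2.05 | 2.05 |
| 10% | 1.97 | 2.02 | 2.02 |
| 20% | 1.91 | 2.02 | 2.02 |
| 40% | 1.77 | 1.98 | 2.00 |

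The 2.05 at 5% is within simulation noise. Expected events are 0.05 × 40,000 = 2,000 and (1 − 0.95²) × 40,000 = 3,900. The standard error of the log ratio is then about √(1/2,000 + 1/3,900) = 0.028, against ln(2.05/2.0) = 0.025. Only Breslow ties at high quit rates attenuate noticeably.

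**3. What does that check leave out?**

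Relapse. Let q be the proportion in an arm who have quit at month 10, r the fraction of them smoking again at month 16, and n the proportion first recorded as quit at month 16. A first-event model counts q + n as quitters by month 16, while status at month 16 gives q(1 − r) + n. The two differ by q·r in each arm. The article gives no figure for r, so the size is unknown.

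**4. Which analysis governs?**

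Blood pressure, harm reduction and quitting each have Cox and a mixed model. Exposure has Cox and a mixed model as well as repeated-measures ANOVA. The later text on aims adds a baseline-adjusted linear mixed model or GEE for cotinine. No sentence ranks them.

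**The case against.** The best reply is that a workable analysis is already there. Generalised linear mixed models cover every outcome indicator, so blood pressure can be analysed and Cox is merely superfluous. That stands, and a reader who inferred that blood pressure has no usable analysis would be going too far. It does not remove the fault: the Cox assignment remains, is repeated, and is not made subordinate.

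A reader might infer that Cox is invalid or cannot be fitted for quitting too. The article does not support this. First recorded quit at month 10 or 16 gives grouped times, and the check above shows little bias with Efron ties or a discrete-time model when there is no relapse. Nor does the article say how a month-10 quitter who relapses would be counted; ignoring relapse is a property of a standard first-event model, not a stated rule. Whether a quit date is recorded cannot be settled here, because the questionnaires are not shown.

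A reader might also infer that the Cox models would ignore clustering and so inflate the type I error. The Cox sentences name no cluster term, but the same section promises estimates adjusted for clustering, an intracluster correlation for each outcome and a multilevel model. A frailty term or robust variance is a detail that a statistical analysis plan may supply. Any figure would also have to carry the ICC of 0.06, assumed in the sample size section, over to other outcomes. No such error rate is claimed.

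Finally, the outcomes are mostly secondary. That is right, and it limits the weight of the point.

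**Conclusion.** The plan is wrong as written for blood pressure values, harm reduction and SHS exposure rates: Cox is prescribed where no event or event time exists. It is also unresolved, because the mixed models cover the same outcomes and neither analysis is given precedence. This follows from the text alone and needs no numerical assumption.

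For quitting the conclusion is weaker. A Cox model is usable but is a poor choice as the main analysis, with two grouped event times and no account of later relapse. The finding of little bias rests on an assumed hazard ratio of 2.0, constant hazards and no relapse.

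The sample size is not affected. The primary outcome is touched only through the phrase about exposure rates, since cotinine has a baseline-adjusted mixed model or GEE that allows for clustering.

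**What to change.** 1. Delete Cox for blood pressure, harm reduction and SHS exposure.
2. State that the mixed models already named govern, with a slum random intercept and baseline adjustment: linear for blood pressure and cotinine, count or linear for cigarettes per day, logistic for yes/no smoking within the home.
3. For quitting, make a mixed-effects logistic model of quit status at each of months 10 and 16 the governing analysis. If a time-to-quit analysis is kept, use a discrete-time complementary log-log model with a slum random effect and define the event, origin, censoring and treatment of relapse.

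The cost is wording only. Table 1 already schedules the measurements these models need, and no change to sample size or visits follows. The Study status section reports baseline collection as ongoing, so, as the article stands, the change can be made before follow-up data exist.

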### Sample size calculation

Based on previous studies we assume an ICC of 0.06.
^
43
^ To detect a minimal difference of 0.03ng/ml in cotinine levels between groups,
^
44
^ at 80% power with a two-sided alfa of 0.05, the estimated sample size was 113 indoor smokers per arm for individual randomization. Since one of the studies in the slum area of Ernakulam had found a prevalence of indoor smoking of 16% and considering slums above 100 households it is assumed that the expected number of smokers within household will be 20 per cluster with variability in clusters. Hence we estimated the sample size for unequal cluster size,
^
45
^ with a CV of 0.45 and VIF=2.4. The estimated sample size was 271 and 14 clusters per arm. Further we assumed a drop-out rate of 10%, the final sample size was rounded to 300 per arm and 15 clusters.

**
*Randomisation*
**

The trial has been registered in Clinical Trials Registry – India
CTRI/2021/06/034478.

A simple randomisation will be undertaken of the selected slums in the urban and peri-urban areas to receive intervention or not by a computer-generated random number list.

Allocation concealment: Allocation will be based on clusters and the allocation will be done after the baseline survey assessment by a statistician not directly related to the study. There is no allocation concealment. All the indoor smokers will be recruited and they will be selected before randomising clusters.

*Implementation*: Meetings will be conducted with the Kochi Corporation and District Medical Office regarding the objectives of the study. After the baseline survey, which will help to identify the indoor smokers, smoking practices, ventilation issues, and waste management practices, a simple randomisation will be undertaken of the selected slums in the urban and peri-urban areas to receive intervention or not.

The allocation sequence generation and the assignment of participants to the intervention will be carried out by the statistician and the investigators will enrol the participants.

*Blinding*: Blinding may not be possible as a lot of people are involved, local self-government officials, the investigators team, health centres, health workers, frontline workers such as the accredited social health activist, and anganwadi workers. The group of people who collect the outcome data will be blinded.

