•To correlate the urinary cotinine levels with the second-hand smoke in the home environment: correlation and linear regression analysis will be carried out by Pearson’s correlation if it follows a normal distribution and Spearman if it is a non-normal distribution.The difference in cotinine levels will be analysed by comparing the urine level of cotinine at the end of follow up, adjusted for the baseline value, by using linear mixed model or GEE to allow for cluster effect.•To measure the effectiveness of the intervention among smokers by measuring their FeV1/FeV6 using COPD6.To determine the effectiveness of the intervention in improvement of lung function the ratio of FeV1/FeV6 will be measured pre- and post-intervention and the mean difference between the groups will be assessed by a paired t-test.
**
*Qualitative data analysis*
**

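### The primary cotinine comparison is given both to a repeated-measures ANOVA without a cluster term and to cluster-adjusted models, and none is named primary

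*Protocol article*

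**What the plan says.** All the places below are in the protocol article.

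- **Outcomes.** The primary outcome is second-hand smoke exposure at 10 and 16 months, "as assessed by the change in mean urine cotinine levels among women and or children of the smoker at the individual level".
- **Outcomes, paragraphs on outcomes and estimation.** "A repeated-measures ANOVA will be used to compare the mean urinary cotinine concentration between groups, before and after intervention". No term for slum is mentioned, and the sentence does not say which ANOVA effect (group, or group by time) is the test.
- **Same paragraphs.** "Generalised linear mixed effect models will be used to test between cluster differences from baseline to each follow up period for each outcome indicator", and then: "A multilevel model will be used for analysis using the generalized linear mixed effect model which will also adjust for individual covariates". Both cover cotinine, since it is one of the outcomes.
- **Outcomes, bulleted aims.** Cotinine at the end of follow-up is to be compared "adjusted for the baseline value, by using linear mixed model or GEE to allow for cluster effect".
- **Sample size calculation.** The individually randomised sample size of 113 per arm is inflated for an ICC of 0.06 and unequal clusters averaging 20, "with a CV of 0.45 and VIF=2.4". This gives 271 people and 14 clusters per arm, raised to 300 and 15 for 10% drop-out.

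The article does not say which of the cotinine analyses answers the primary question.

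**The concern.** The ANOVA sentence describes the trial's main comparison. As written, it treats residents of the same slum as independent, although the sample size more than doubles because they are not. Where the authors intend to handle clustering they say so, as in the LMM or GEE sentence and in the word multilevel. The ANOVA sentence has no such qualifier.

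The second problem is the coexistence of several analyses. The ANOVA compares groups over the visits, the mixed models address change from baseline to each follow-up, and the LMM or GEE addresses the end value given baseline. Even where two of them aim at the same mean difference at the same visit, they give different estimates when the arms differ at baseline. The article itself expects chance imbalance with few clusters.

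With no primary analysis named, the method can be chosen after the results are seen, and one of the candidates may not hold its 5% level.

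**Working it through.** **Inputs from the Sample size calculation section.** ICC 0.06, mean cluster size m = 20, cluster-size CV 0.45, 113 per arm before inflation, two-sided alpha 0.05, 10% drop-out.

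**Step 1: reproduce the plan's figures.**
- VIF = 1 + ((1 + CV²) × m − 1) × ICC = 1 + (1.2025 × 20 − 1) × 0.06 = 1 + 23.05 × 0.06 = 2.383, stated as 2.4.
- 113 × 2.4 = 271.2 (stated 271), and 271.2 / 20 = 13.6, so 14 clusters.
- 271 / 0.9 = 301, stated as rounded to 300.

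The plan's figures reproduce.

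**Step 2: one between-group comparison at one visit, ignoring slums.** The standard error is too small by a factor √VIF = √2.4 = 1.55. The actual type I error is 2 × (1 − Φ(1.96 / √VIF)).

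| ICC | VIF | Actual type I error |
|---|---|---|
| 0.06 (plan, VIF as stated) | 2.4 | 20.6% |
| 0.06 (plan, VIF unrounded) | 2.383 | 20.4% |
| 0.03 (assumed) | 1.69 | 13.2% |
| 0.02 (assumed) | 1.46 | 10.5% |

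**Step 3: the group-by-time test.** A test of groups before and after the intervention is naturally read as group by time. A slum effect that stays constant cancels from a change, so what matters is the correlation of a slum's effect between visits (the autocorrelation, r). The article gives no value for r. For a change between two visits with assumed within-person correlation w, the ICC of the change is

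ICC(1 − r) / [ICC(1 − r) + (1 − ICC)(1 − w)].

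With ICC 0.06 and w = 0.5:
- r = 0.9: 0.006 / (0.006 + 0.47) = 0.0126, VIF 1.29, type I error 8.4%.
- r = 0.8: 0.012 / (0.012 + 0.47) = 0.0249, VIF 1.57, type I error 11.8%.
- r = 0.5: 0.030 / (0.030 + 0.47) = 0.06, VIF 2.38, type I error 20.4%.

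**Step 4: simulate the ANOVA itself.** Two groups, three visits, 30 slums, mean size 20, CV 0.45, ICC 0.06, w = 0.5, no true effect, no cluster term, 3,000 runs per setting. The Monte Carlo standard error near 20% is √(0.2 × 0.8 / 3000) = 0.7 percentage points.

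| Autocorrelation r (assumed) | Single follow-up comparison | ANOVA group effect | ANOVA group-by-time |
|---|---|---|---|
| 1.0 | 20.5% | 25.4% | 5.0% |
| 0.9 | 20.3% | 25.0% | 10.7% |
| 0.8 | 20.6% | 24.5% | 15.0% |
| 0.5 | 21.4% | 19.4% | 28.1% |
| 0 | 20.9% | 13.2% | 43.5% |

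The three-visit interaction test has two degrees of freedom, so its error is larger than that of the two-visit change in Step 3 whenever r is below 1. Under the same inputs, a t-test on slum means at one visit held about 5%.

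**The case against.** The strongest reply is that clustering is not overlooked. The article plans mixed models for every outcome and a multilevel model for the analysis. It also plans an LMM or GEE for cotinine that explicitly allows for the cluster effect, and ICC reporting for each outcome. Of the cotinine tests named, only the ANOVA lacks a cluster-aware method. The planned 95% confidence interval for the difference in means is not tied to the ANOVA and can be read as a cluster-level comparison. This stands: the trial's inference is invalid only if it rests on the ANOVA, and the article does not say that it will.

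A reader might infer from "Adjusted estimates of clustering will also be provided" that cluster adjustment is merely an add-on. The unqualified sentences about the multilevel model and the mixed models do not support that.

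A second reply is that 20% belongs to a comparison at one visit, whereas the ANOVA sentence most naturally describes group by time. This also stands. For that test the error may be close to 5% or well above 20%, depending on a quantity the article does not give.

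A reader might also see a clash between an ANOVA that needs complete visits and "We will use an intention to treat approach in analysis". That is a general statement of approach, and handling of missing visits is commonly left to an analysis plan, so it does not carry this point.

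Finally, a Gaussian generalised linear mixed model is a linear mixed model, so the planned models form fewer families than a count of sentences suggests. Their contrasts still differ.

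None of this removes the conflict. A stated method does not fit the design, and an analysis plan that chose another method would have to overrule a sentence of the protocol.

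**Conclusion.** The point holds as an unresolved conflict over the primary analysis that includes one method unsuited to cluster randomisation. It does not hold as a claim that the trial ignores clustering, or that its main test will run at 20%.

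The size is conditional on inference resting on the ANOVA. About 20% applies to a single between-group comparison at the plan's ICC of 0.06. For the group-by-time test the range is about 5% (slum effects fully stable) to 28% (autocorrelation 0.5), and higher if slum effects are less stable still. That range rests on assumed autocorrelations, an assumed within-person correlation of 0.5 and the plan's own ICC, cluster size and CV. The ANOVA's validity would therefore depend on which effect is tested and on slum effects staying fully stable.

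**What to change.** Delete the repeated-measures ANOVA sentence. Name one cluster-adjusted analysis already in the protocol as primary, and state the visit or visits to which it applies, since the primary outcome names both 10 and 16 months. One suitable choice is the baseline-adjusted linear mixed model with a random effect for slum and a small-sample correction for 30 clusters. Label any other model, including GEE if kept, as a sensitivity analysis. The exact degrees-of-freedom method and any further random effects (person, household) can be left to the analysis plan.

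The cost is wording only, with no new data, visits or participants. Intervals will be wider than the ANOVA's where slum effects matter, but valid. The article's study status section reports baseline collection still under way, so on that status the choice can be fixed before outcome data exist.
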